### Group 2 (constant intensity, control A)

Firstly, individuals will perform a global warm-up of four unloaded exercises: seated calf raise (1 min), lateral dumbbell raise (1 min), leg press (1 min), and incline bench press (1 min) [69, 70]. They will then perform moderate intensity resistance training (50% of maximum dynamic strength). Individuals will work nine muscle groups (gluteus, quadriceps, hamstrings, biceps brachii, triceps brachialis, pectoralis, calf, deltoid, and latissimus dorsi) through six different exercises in the following order: seated calf raise, knee extension machine, leg press, incline bench press, seated row machine, and dumbbell lateral raise [21].

Based on 50% of the maximum dynamic strength as the initial parameter for moderate intensity in resistance training, the load in kg will be previously identified through the 1-RM test in the proposed exercises. The muscular strength of each individual will be individually reassessed every 4 weeks (via 1-RM) and the intensity (total load in kg) will be maintained at 50% of the maximum dynamic strength until the end of the complete treatment (i.e., constant intensity from month 1 to month 3 – Table 2) [17, 21].

The intensity of the exercises (total load in kg), the interval among sets (rest in seconds), the volume (number of sets, repetitions and time under tension) as well as the frequency of the resistance training will be controlled by the researcher with experience in chronic pain. Twice a week (for 3 months), individuals with fibromyalgia will perform three sets of each exercise: 10 repetitions, 40 s of muscle tension, full range of motion, inspiration during the eccentric phase of the movement, and 60 s of rest among sets. [71].

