## Abstract

**Background:**

Fibromyalgia guidelines indicate that exercise is critical in the management of fibromyalgia, and there is evidence that patients with fibromyalgia can perform resistance training at moderate and high intensities. However, despite the biological plausibility that progression of intensity provides greater benefit to individuals, no studies have compared different intensities (progressive versus constant intensities) of the same exercise in this population.

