**Methods:**

A protocol for a blinded randomized controlled trial. The sample will be randomized into three groups: group 1 (progressive intensity, experimental), group 2 (constant intensity, control A), and group 3 (walking, control B). Group 1 will perform resistance training at moderate intensity (50% of maximum dynamic strength), previously determined by the 1 repetition maximum (1-RM) test in the proposed exercises. The strength of each individual will be reassessed every 4 weeks (by 1-RM) and the intensity of each exercise will be positively adjusted by 20% of the value observed in kg (i.e., first month 50%; second month 70%; third month 90% of the maximum dynamic strength). Group 2 will perform the same procedure, but the intensity will be maintained at 50% of the maximum dynamic strength throughout the treatment (i.e., constant intensity from the first to the third month). Group 3 will perform a 40-minute treadmill walk at low intensity, defined by a walking speed corresponding to 60-70% of the maximum heart rate, which we will control with a heart rate monitor. All groups will receive a 45-minute pain education session prior to the exercise program, covering the pathophysiologic mechanisms of chronic pain, strategies for coping with pain, avoiding hypervigilance, and deconstructing beliefs and myths about chronic pain.

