### Outcomes

Primary outcome will be the comparison (among groups) of the effect of 24 sessions of resistance training (progressive intensity vs. constant intensity) on impact of fibromyalgia. Secondary outcomes will be to evaluate changes in sleep quality, anxiety, depression, cutaneous sensory threshold, wind-up mechanism, diffuse nociceptive inhibitory control, walking ability, musculoskeletal capacity after 24 sessions of resistance training, as well as global perceived effect and adherence regarding treatment and impact of fibromyalgia during the intervention and after 3 months of non-exercise follow-up (Fig. 2).

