### Group 1 (Progressive intensity, experimental)

Firstly, individuals will perform a global warm-up of four exercises (Fig. 3) without load: seated calf raise (1 min), lateral dumbbell raise (1 min), leg press (1 min), and incline bench press (1 min) [69, 70]. They will then perform moderate intensity resistance training (50% of maximum dynamic strength). Individuals work nine muscle groups (gluteus, quadriceps, hamstrings, biceps brachii, triceps brachii, pectoralis major, calf, deltoid, and latissimus dorsi) through six different exercises in the following order: seated calf raise, knee extension machine, seated row machine, dumbbell lateral raise, leg press, and incline bench press [21].

Based on 50% of the maximum dynamic strength as the initial parameter for moderate intensity in resistance training [17, 21], the load in kg will be previously identified through the 1-RM test in the proposed exercises. The individual’s muscular strength will be individually reassessed every 4 weeks (via 1-RM) and the intensity of each exercise will receive a positive adjustment of 20% of the value observed in kg (i.e., first month 50%; second month 70%; third month 90% of the maximal dynamic strength – Table 2) [17, 21].

**Table 2 Tab2:** Description of the intensity of physical exercise programs

Group (intensity)	1st Month	2nd Month	3rd Month	Follow-up
1. Progressive intensity (experimental)	50% (1-RM test)	70% (1-RM test)	90% (1-RM test)	Nonexercise
2. Constant intensity (control A)	50% (1-RM test)	50% (1-RM test)	50% (1-RM test)	Nonexercise
3. Walking (control B)	60-70% (HRmax)	60-70% (HRmax)	60-70% (HRmax)	Nonexercise

1-RM test: 1-repetition maximum test; HRmax: maximum heart rate. The external load (intensity) will be adjusted on the basis of the new values observed in the 1-RM (every 4 weeks)

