The intensity of the exercises (total load in kg), the interval between sets (rest in seconds), the volume (number of sets, repetitions and time under tension) as well as the frequency of the resistance training will be controlled by the researcher with experience in chronic pain. Twice a week (for 3 months), individuals with fibromyalgia will perform three sets of each exercise: 10 repetitions, 40 s of muscle tension, full range of motion, inspiration during the eccentric phase of the movement, and 60 s of rest among sets [71]. In order to maintain the same volume of exercises in resistance training (according to the intensity progression), we will add 20 s of rest to the rest among sets (i.e., first month 60; second month 80; third month 100 s of interval), because higher intensities, while maintaining the same volume of work (sets, repetitions, and time under tension), require longer intervals of rest [72].

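### The two resistance arms are given different exercise orders with no reason stated; if both are followed, order cannot be separated from progression of intensity

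*Protocol article*

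**What the plan says.** The section on Group 1 (progressive intensity) says that participants do six exercises "in the following order: seated calf raise, knee extension machine, seated row machine, dumbbell lateral raise, leg press, and incline bench press". The section on Group 2 (constant intensity) likewise says that they do six exercises in a set order: "seated calf raise, knee extension machine, leg press, incline bench press, seated row machine, and dumbbell lateral raise". Both lists are worded as a prescribed sequence, and both cite the same source.

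The abstract's Methods paragraph states: "Group 2 will perform the same procedure, but the intensity will be maintained at 50% of the maximum dynamic strength throughout the treatment". The abstract's Background gives the gap that the trial is to fill: "no studies have compared different intensities (progressive versus constant intensities) of the same exercise in this population". The Outcomes section then makes this the primary comparison: "Primary outcome will be the comparison (among groups) of the effect of 24 sessions of resistance training (progressive intensity vs. constant intensity").

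Besides load, one further difference between the resistance arms is stated openly. For Group 1, "we will add 20 s of rest to the rest among sets (i.e., first month 60; second month 80; third month 100 s of interval"), on the ground that higher intensity needs longer recovery. The Group 2 section gives 60 s and no increase.

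**The concern.** The trial exists to tell whether progressing the intensity of a given resistance programme does more than holding it constant. That reading requires the two programmes to match in everything except intensity and whatever is openly tied to it. Here a second, unexplained feature of the sessions also differs between the arms.

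At stake is attribution. If a difference in FIQ-R appears, or fails to appear, the authors would want to ascribe it to progression. With a different exercise sequence in each arm, they could strictly ascribe it only to the package of progression, longer rest and sequence. Randomization does not protect against this, because the sequence is part of the assigned treatment and not a participant characteristic.

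The article also says that it describes the intervention with a template meant to allow replication. Anyone repeating the trial would not know whether the two sequences are intended.

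**Working it through.** The point rests on no sample-size or power figure, so there is no stated figure to reproduce. The check has three steps.

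**1. Compare the lists position by position** (inputs: the Group 1 and Group 2 sections).

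| Exercise | Position, Group 1 | Position, Group 2 | Shift |
|---|---|---|---|
| Seated calf raise | 1 | 1 | 0 |
| Knee extension | 2 | 2 | 0 |
| Seated row | 3 | 5 | +2 |
| Lateral raise | 4 | 6 | +2 |
| Leg press | 5 | 3 | −2 |
| Incline bench press | 6 | 4 | −2 |

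The set of exercises is identical. Four of six positions differ, and they differ in a simple way: the pair row and lateral raise has changed places with the pair leg press and bench press, and the order inside each pair is kept.

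**2. List what else differs between the resistance arms.**

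| Element | Group 1 | Group 2 | Reason given? |
|---|---|---|---|
| Load, months 1/2/3 | 50/70/90% of 1-RM | 50/50/50% of 1-RM | Yes, the question under study |
| Rest between sets, months 1/2/3 | 60/80/100 s | 60 s, no increase stated | Yes, tied to load |
| Warm-up, sets, repetitions, time under tension, frequency | same | same | not needed |
| Exercise order | as above | as above | No |

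**3. Ask whether the analysis could separate order from arm.** Among the resistance participants, let P = 1 for progressive and 0 for constant, and let O = 1 for the Group 1 sequence and 0 for the Group 2 sequence. If the lists are followed, O = P for every one of the 21 + 21 = 42 planned participants, in each of the 24 sessions. The two columns of the design matrix are identical, so the progressive-versus-constant contrast estimates

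effect of progression (with its longer rest) + effect of order,

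and only the sum is identifiable. Adding baseline as a covariate or a group-by-time interaction, as the Statistical analysis section plans, does not change this, because order never varies within an arm. The walking arm has no resistance sequence and so carries no information about it.

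The first month does not help either. Load (50%) and rest (60 s) are then the same in both arms, so order would be the only prescribed difference. But FIQ-R is measured at weeks 1, 6, 12 and 24, and week 6 falls in the second month, after loads have diverged. No FIQ-R assessment isolates order.

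**The case against.** Four objections deserve weight.

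*It may be a slip.* Two adjacent pairs are exchanged and everything else matches. The Intervention overview speaks of a single resistance programme, shown in one exercise figure that is not available here. No sentence states an intention to vary order. If both arms in fact use one sequence, there is no bias, only a line to correct. This stands: a reader might infer that the primary contrast is confounded as a matter of fact, but the documents support that only on condition that both lists are followed.

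*The arms already differ in more than intensity.* This stands too. A reader might take it that intensity alone was meant to differ, but the longer rest in Group 1 is an openly planned second difference. The distinction is that rest is declared and tied to load, and order is neither.

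*The abstract may promise less than it seems.* Its remark that Group 2 does the same as Group 1 follows sentences on the 1-RM test and the reassessment of strength, so it can be read as referring to how load is set. That is a fair reading, and it softens the conflict with the abstract. It does not touch the conflict between the two lists, and the Background still frames the question as different intensities of one exercise.

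*No mechanism is shown.* A reader might infer that fatigue or the load achieved must differ systematically between the arms. The documents do not show this. Load is prescribed from a 1-RM test in each exercise, with sets and repetitions fixed, so order does not alter the prescription. Nothing in the article links within-session order to a questionnaire with a 7-day recall. This limits the point to an unknown and possibly small effect.

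**Conclusion.** The concern holds in a conditional form. It is certain that the two sections prescribe different sequences in positions 3 to 6 and that no reason is given. If both are followed, order is completely aliased with the progressive-versus-constant comparison, and no model can remove it. The comparison of progressive training with walking is not affected in this way, because whole programmes are compared there.

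The size and sign of any resulting bias in FIQ-R cannot be derived from the documents. Four of six positions in 24 sessions describes how far the lists disagree; it is not a measure of bias. The conclusion assumes that the lists are printed as the authors wrote them and that each is meant as the fixed order for its arm, as both sections say. Whether the mismatch is deliberate or a slip is not known.

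**What to change.** Reconcile the Group 1 and Group 2 sections, and check the exercise figure against them, so that both resistance arms follow one order. Which order is for the investigators to choose.

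If the mismatch is only a slip in the text, or nobody has yet been treated, the cost is one corrected line and no added burden for participants. The article does not give recruitment status. If participants have already trained under different orders, state this in the protocol and the trial report, and limit the conclusion: a difference between the resistance arms should then be described as a difference between two programmes, not credited to intensity progression alone.

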### Group 3 (walking, control B)

Individuals will walk on the treadmill for 40 min at an intensity determined by the walking speed corresponding to 60-70% of the maximum heart rate (HRmax), which will be estimated (in advance for each individual) by the mathematical equation: HRmax = 220 - age (in years) and recalculated if the individual has a birthday during the treatment period [67]. As such, the individual is verbally motivated to walk at a constant pace to keep the heart rate around 60-70% of HRmax (Table 2).

To ensure stabilization of low intensity, if the individual exceeds 60–70% of HRmax, we slowly reduce the treadmill speed until the heartbeats reach 60-70% of HRmax (considering the standard error of estimation of up to 10 heartbeats for more or less) [67]. Heart rate is monitored using a Polar V800 heart rate monitor (Polar Electro OU®, Kempele, Finland) with a sensor attached to the subject’s chest. This device has been used in studies of chronic pain [73, 74].

### Statistical analysis

We will perform statistical analysis based on intention-to-treat analysis. We will use histograms and normality tests to verify the distribution of the data. Comparisons will be made through mixed linear models using interaction between factors time (before, during the intervention, after 24 exercise sessions, and 3 months after the end of treatment) and group (progressive intensity, constant intensity, and walking), besides, the baseline will be used as a covariate in the analyses [75]. Data will be presented as mean, standard-deviation, difference between means, confidence interval (95%) of these differences, and effect size (Cohen d). We will consider a significance level of 5% on the SPSS® software, version 17.0 (Chicago, IL, EUA) [76].

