### Sample size

We performed the sampling using Ene 3.0 and G*Power 3.1.9.7 software, considering the comparison of three independent groups (progressive intensity [n = 21]), group 2 (constant intensity [n = 21]), and group 3 (walking [n = 21]) at four different stages (before, during the intervention, after 24 exercise sessions, and 3 months after the end of treatment) by ANOVA for repeated measures. We chose impact of fibromyalgia as the primary outcome variable, measured by the Revised Fibromyalgia Impact Questionnaire (FIQ-R). We based the calculation on detecting the minimum clinically important difference of 27 points between independent groups (Ene) [36], standard-deviation of 16.3 points (Ene) [37], statistical power of 95% (G*Power), significance of 5% (both), effect size of 0.41 (G*Power) [38, 39], and sample loss of 15% (Ene). Thus, the sample must contain 21 individuals per group (total = 63).

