### Impact of fibromyalgia

We will assess the impact of fibromyalgia using the FIQ-R, an instrument validated for the Brazilian population by Lupi et al. (2016) [42], with adequate reliability and internal consistency [43]. The FIQ-R is used for assessments at week 1, 6, 12, and 24. It consists of 21 items assessing function (items 1–9), global impact (items 10–11), and symptoms (items 12–21). All questions relate to experiences during the past 7 days and are presented on an 11-point numerical rating scale (from 0 to 10). A normalization factor is applied to each of the three domain scores: the functional domain score is divided by 3, the global impact domain score is divided by 1, and the symptom domain score is divided by 2. The total FIQ-R score (from 0 to 100) is obtained by summing the three normalized domain scores. Thus, the lower the score, the lower the impact of fibromyalgia on the individual’s overall quality of life. A reduction of 27 points is considered to be the minimum clinically important difference [36], although this may change in new studies [43].

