### Global perceived effect regarding treatment

We will assess the self-reported global perceived effect of treatment using the Global Perceived Effect (GPE) scale, an instrument validated for the Brazilian population by Costa et al. [65]. It is an 11-point descriptive scale in which the progression (or regression) of the individual’s clinical condition is classified according to their score at a given time. Thus, the individual will report their perception of improvement in the face of the intervention through a score classified as: -5 (much worse), 0 (no change), and + 5 (fully recovered). We will use the GPE at three assessments (6th, 12th, and 24th week). A change of 3 points is considered a clinically important minimum difference.

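### Baseline is both a response and a covariate in the same mixed model; depending on the contrast reported, the week-12 comparison is anti-conservative, the adjustment is wasted, or the model cannot be fitted

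*Protocol article*

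**What the plan says.** The Statistical analysis section of the protocol article specifies "mixed linear models using interaction between factors time (before, during the intervention, after 24 exercise sessions, and 3 months after the end of treatment", crossed with group, and continues: "besides, the baseline will be used as a covariate in the analyses". The first level of time is thus the pre-treatment measurement, and nothing in the article removes it from the responses.

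Other sections also count four occasions. Under Impact of fibromyalgia: "The FIQ-R is used for assessments at week 1, 6, 12, and 24". Under Sample size the three groups are compared "at four different stages (before, during the intervention, after 24 exercise sessions, and 3 months after the end of treatment) by ANOVA for repeated measures".

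Under Outcomes the target is the between-group result once training is complete: "Primary outcome will be the comparison (among groups) of the effect of 24 sessions of resistance training". The Statistical analysis section also promises mean differences with 95% confidence intervals. It does not say which contrast from the model carries the primary conclusion.

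**The concern.** A baseline value can be an outcome in a longitudinal model, or it can be a covariate for the later visits. In both roles at once, the baseline row of each participant is regressed on itself. Three things can then go wrong:

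- The shared baseline slope is pulled towards 1, and the artificially small baseline residuals lower the pooled variance. An adjusted group difference at a later visit then looks more precise than it is.
- A covariate that is constant within a person drops out of within-person contrasts, so the interaction gets no benefit from the adjustment.
- If each visit has its own variance, the baseline variance can be driven to zero.

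At stake is whether the week-12 comparison keeps its 5% error rate, and whether baseline adjustment delivers the precision it was included for.

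**Working it through.** **Inputs from the article.** Three groups, 1:1:1, 21 each; four FIQ-R visits; SD 16.3; design difference 27 points; 15% loss; 5% significance ("We will consider a significance level of 5% on the SPSS® software, version 17.0"). After loss, 21 × 0.85 = 17.85, or about 18 per arm.

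**Assumptions, not in the article.** Two-sided testing; between-visit correlation ρ of 0.3, 0.5 or 0.7; equal variances over time; illustrative true differences of 10 and 14 points.

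**The article's own figure.** For the between-groups repeated-measures calculation, λ = f²·N·m / (1 + (m − 1)ρ). With f = 0.41, N = 63, m = 4 and ρ = 0.5, λ = 0.1681 × 63 × 4 / 2.5 = 16.94 and power is 0.958. So 63 is reproduced at ρ = 0.5, before any allowance for loss. This makes 0.5 a reasonable central value below; it has no other bearing on this point.

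**(a) Adjusted week-12 difference, random intercept (compound symmetry).** In units of SD²:

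- Common slope: β = (1 + 3ρ)/4, where a week-12 regression would give ρ.
- Baseline residual variance: (1 − β)².
- Residual variance at each later visit: 1 − 2βρ + β².
- Variance used by the model: the average over the four visits.

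At ρ = 0.5: β = 0.625; baseline (0.375)² = 0.141; later visits 1 − 0.625 + 0.391 = 0.766; average (0.141 + 3 × 0.766)/4 = 0.609. The ratio is 0.609/0.766 = 0.80. The nominal cut-off of 1.96 acts like 1.96 × √0.796 = 1.75, a two-sided size of 8.0%. With 18 per arm the model SE is √(0.609 × 2/18) = 0.260 SD, against a true √(0.766 × 2/18) = 0.292 SD.

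| ρ | β | model variance | true variance | large-sample size | simulated, 21 per arm | simulated, 18 per arm | simulated, post-baseline responses only (21 per arm) |
|---|---|---|---|---|---|---|---|
| 0.3 | 0.475 | 0.774 | 0.941 | 7.5% | 7.4% | 7.0% | 4.9% |
| 0.5 | 0.625 | 0.609 | 0.766 | 8.0% | 7.8% | 8.1% | 4.7% |
| 0.7 | 0.775 | 0.399 | 0.516 | 8.5% | 8.9% | 8.6% | 5.0% |

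The simulations at 21 per arm used 10,000 null trials per setting, REML and Satterthwaite degrees of freedom. Fitting a homogeneous AR(1) structure instead gave 7.7% to 8.2%.

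**(b) Group-by-time interaction.** In complete data the test is the same with and without the covariate. At ρ = 0.5 the rejection rate was 5.54% in both under the null and 64.98% in both at a 14-point difference. Null size was 5.2%, 5.5% and 4.7% at ρ = 0.3, 0.5 and 0.7. The baseline-to-week-12 contrast has variance proportional to 2(1 − ρ), against 1 − ρ² for ANCOVA:

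| ρ | 2(1 − ρ) | 1 − ρ² | variance removed by ANCOVA |
|---|---|---|---|
| 0.3 | 1.40 | 0.91 | 35% |
| 0.5 | 1.00 | 0.75 | 25% |
| 0.7 | 0.60 | 0.51 | 15% |

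Power at 18 per arm, ρ = 0.5, 10 points: the contrast SE is 16.3 × √(1.00 × 2/18) = 5.43, so 10/5.43 = 1.84, about 44-46%. The ANCOVA SE is 16.3 × √(0.75 × 2/18) = 4.71, so 10/4.71 = 2.13, about 55%. At 27 points and ρ = 0.3, the least favourable case, the contrast SE is 16.3 × √(1.40 × 2/18) = 6.43 and 27/6.43 = 4.20. Both analyses then exceed 98%.

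**(c) Time-specific variances.** As the slope approaches 1 the baseline residuals vanish and the log-likelihood rises without limit. In one simulated data set with an unstructured covariance it was −723 at slope 0.625, −495 at 0.99 and −60 at 0.99999. A diagonal covariance behaves in the same way.

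**The case against.** The strongest reply is that the only test the section names is the interaction, and that test is valid: its size is about 5% with or without the covariate. Inflation needs two further steps, namely reading an adjusted week-12 difference from the four-response model and using a common-variance structure. The article states neither, and the covariance structure is properly left to an analysis plan. This stands. A reader might infer that the trial's primary test has an inflated error rate as planned; the article does not support that. Route (a) is nevertheless plausible, because mean differences with confidence intervals are promised and the primary outcome concerns the end of training. Outcomes (a) and (c) arise under different covariance structures and cannot both occur.

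A reader might also infer a serious loss of power. At the article's own 27 points there is practically none; the loss matters only for smaller true differences. Nor is it exact to say that the covariate contributes nothing. That holds for complete data. With about 15% dropout, a small check of 25 fits at ρ = 0.5 showed the interaction standard error falling by about 1%.

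Finally, the Global Perceived Effect has no pre-treatment value ("We will use the GPE at three assessments (6th, 12th, and 24th week"), so a baseline term cannot apply to it. Dropping an inapplicable term is routine detail for an analysis plan and is not counted here.

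The authors may have meant post-baseline visits with baseline as covariate. The written time factor, "interaction between factors time (before, during the intervention, after 24 exercise sessions, and 3 months after the end of treatment", says otherwise, so the sentence needs correcting even on that reading.

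**Conclusion.** The model as written gives baseline two incompatible roles. This is an error in the stated model, not a detail left to another document. Its effect is conditional:

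- Adjusted week-12 difference under random intercept, compound symmetry or AR(1): type I error about 7-9% instead of 5%, so a nominal 95% interval covers about 91-93%.
- Interaction: size near 5%, but with complete data the adjustment is wasted and the baseline-to-week-12 contrast keeps change-score variance.
- Unstructured or diagonal covariance: no proper maximum of the likelihood.

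These figures rest on an assumed ρ of 0.3-0.7, two-sided testing, 18-21 per arm and "baseline" meaning the baseline value of the outcome. Severity: should fix. A valid reading exists and power at the design difference is unaffected, but leaving the contrast open allows a choice between tests with different error rates.

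**What to change.** Replace the model sentence with one of two specifications:

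1. Responses at weeks 6, 12 and 24 only; fixed effects for group, visit, group by visit, baseline FIQ-R and baseline by visit; the adjusted group difference at week 12 named as the primary contrast.
2. All four visits as responses, with the baseline mean constrained to be equal across groups and no baseline covariate; the week-12 group difference as the primary contrast.

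For outcomes measured only at weeks 1 and 12 (6-minute walk test and isokinetic dynamometry), use ANCOVA at week 12.

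The cost is about two sentences in the statistical section, settled before the data are analysed. No new data, visits or participants are needed. In the simulations, the first specification (fitted without the baseline-by-visit term) brought the week-12 test back to 4.7-5.0%.
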